## Abstract

**Background:**

Cervical radicular syndrome (CRS) due to a herniated disc can be safely treated by surgical decompression of the spinal root. In the vast majority of cases this relieves pain in the arm and restores function. However, conservative treatment also has a high chance on relieving symptoms. The objective of the present study is to evaluate the (cost-) effectiveness of surgery versus prolonged conservative care during one year of follow-up, and to evaluate the timing of surgery. Predisposing factors in favour of one of the two treatments will be evaluated.

**Methods/design:**

Patients with disabling radicular arm pain, suffering for at least 2 months, and an MRI-proven herniated cervical disc will be randomised to receive either surgery or prolonged conservative care with surgery if needed. The surgical intervention will be an anterior discectomy or a posterior foraminotomy that is carried out according to usual care. Surgery will take place within 2–4 weeks after randomisation. Conservative care starts immediately after randomisation. The primary outcome measure is the VAS for pain or tingling sensations in the arm one year after randomisation. In addition, timing of surgery will be studied by correlating the primary outcome to the duration of symptoms. Secondary outcome measures encompass quality of life, costs and perceived recovery. Predefined prognostic factors will be evaluated. The total follow-up period will cover two years. A sample size of 400 patients is needed. Statistical analysis will be performed using a linear mixed model which will be based on the ‘intention to treat’ principle. In addition, a new CRS questionnaire for patients will be developed, the Leiden Cervical Radicular Syndrome Functioning (LCRSF) scale.

**Discussion:**

The outcome will contribute to better decision making for the treatment of cervical radicular syndrome.

**Trial registration:**

NTR3504

## Background

The cervical radicular syndrome (CRS) caused by a cervical hernia nuclei pulposus (HNP), is a frequently occurring problem with an incidence of 0.8 per 1000 inhabitants per year and a prevalence of 3.5 per 1000 inhabitants [1,2]. CRS can lead to invalidating radicular pain and may lead to motor and sensory deficits [1,3]. In the majority of patients the symptoms gradually diminish within weeks to such an extent that normal daily activities can be continued [4-6].

Many controversies exist regarding the timing of diagnostic procedures, the timing of referral of patients to the neurologist or neurosurgeon and the timing of a surgical intervention for a cervical HNP [7]. Nowadays, the timing of an elective surgical intervention is not based on scientific knowledge, but on the preference of the individual neurologist and neurosurgeon and local production capacity.

A previous Dutch randomised controlled trial (RCT) compared different conservative strategies in patients with a short term CRS (at least 3 weeks pain in the arm). In all strategy arms the median visual analogue scale (VAS) pain in the arm decreased from 68–72 to 20–25 mm (range 0–50 mm) within six months [6]. Moreover, indirect evidence indicates that most cervical disc protrusions resolve spontaneously without surgery [6,8-11]. If complaints do not diminish spontaneously within reasonable time, surgery can be considered. Surgical intervention is usually performed by an anterior discectomy with subsequent anterior decompression of the spinal nerve. The effectiveness (pain relief, satisfaction, muscle weakness improvement) of the anterior discectomy to reduce symptoms is demonstrated to be between 80 and 95%, and the procedure has been established as a safe intervention [12-17]. Another approach to decompress the spinal nerve is a posterior foraminotomy which has a positive outcome in 75 to 95% of the cases [18]. Both conservative care and surgical intervention are successful treatments, but it is unknown which patients benefit most from each strategy [7-9,19]. Only two small RCTs have been performed; Persson *et al.* demonstrated that pain, function and mood after one year of follow-up was equal in the conservative and surgical group [20]. However, this was a small trial with 54 patients in the conservative and 27 patients in the surgery group and the power was estimated to be only 47%. Engquist *et al.* demonstrated that a higher percentage of patients that were operated (n = 31) rated their symptoms as ‘better’, than in the conservatively treated group (n = 32). This difference disappeared at the two year evaluation moment [21]. In both trials, timing of surgery was not studied, and no cost-effectiveness or predisposing factors were evaluated. Furthermore, two nonrandomised studies have been published; in one study (n(surgery) = 39; n(conservative) = 21) the outcomes were in favour of the conservative group after 5.5 years [22] while the other study (n (surgery) = 51; n (conservative) = 104) showed better results for the surgery group after 1 year follow-up [23]. However, the surgical group in both studies had more pain and worse functional scores at baseline, which excludes adequate outcome comparison.

No studies have been published regarding the cost-effectiveness of conservative and surgical therapy. In the Netherlands, on average 2000 patients yearly receive surgery for a cervical herniated disc, resulting in direct costs of about €30 million per year. Although direct costs for conservative care are lower, this group might have higher indirect costs due to a longer period of reduced labour productivity. Further research on cost-effectiveness could lead to reduction of costs for healthcare and society.

The primary goal of the present study is to compare the (cost-) effectiveness of conservative therapy for cervical HNP, sometimes followed by ‘late’ surgery if needed, with early surgical intervention. The timing of surgery will be studied, and several predisposing factors will be analysed. In addition to the trial, the participants will also participate in the development and validation of an outcome scale for CRS, the Leiden Cervical Radicular Syndrome Functioning (LCRSF) scale.

## Methods

### Design

The present study is a multi-centre patient-randomised controlled trial with parallel group design. The main research question will be answered after one year of follow-up and the complete follow-up will last two years. The Medical Ethics Committee of the Leiden University Medical Centre has approved the study protocol. Every participating centre independently has given approval before including patients. Informed consent will be obtained from all participating patients. The study was registered July 3, 2012 in the Dutch Trial register (NTR3504).

### Patients

All patients (18–75 yr.) with CRS and at least 2 months of disabling pain or tingling sensations will be eligible for participation. Either the VAS arm pain or the VAS tingling sensations should be more than or equal to 40 mm. MRI must confirm the presence of a herniated cervical disc as explanation for the symptoms. The inclusion and exclusion criteria are shown in Table 1.

**Table 1 T1:** Inclusion and exclusion criteria

Inclusion criteria	age 18–75 years
	at least two months existing complaints of radicular sensations in the arm (VAS arm pain or VAS tingling sensations) of at least 40 mm
	herniated disc with root compression confirmed by MRI corresponding with the clinical symptoms
	signed informed consent
Exclusion criteria	paresis of MRC <4
	mainly signs of myelopathy
	any form of cervical spine surgery in the past
	instability of the cervical spinal column requiring stabilisation
	pregnancy
	insufficient knowledge of Dutch language
	planned emigration in the year after randomisation
	participation in another clinical trial

### Baseline data

The baseline questionnaires and demographics will be registered before randomisation. Also the preferences of patients and doctors will be registered using a 5-point scale varying from ‘strong preference for surgery’ to ‘strong preference for conservative treatment’.

### Randomisation procedure

A randomisation list is prepared for every participating hospital. Randomisation will take place in variable permutation blocks, which are unknown to the research nurse. A random generator is used to generate the random sequence within the blocks. The data manager, who is not involved in the selection and allocation of patients, will prepare coded and sealed envelopes containing the treatment allocation based on the pre-generated stratified random allocation list.

The research nurse will make an appointment with the participant after the visit to the neurologist or neurosurgeon. After registering baseline information, a sealed envelope with treatment allocation will be opened in front of the patient. Patients who do not wish to be randomised will be asked to participate in a cohort study, in which both surgically and conservatively treated patients will be followed.

### Interventions

#### Group A: Surgical intervention

Surgery will take place within 2–4 weeks of randomisation. ‘Usual care’ will be pursued. Therefore the surgeon can perform the surgery he prefers, with the exception of implantation of an artificial disc. Variables of the procedure are filled in a standardised form.

For anterior discectomy, the level of surgery is verified by fluoroscopy. The operation will be carried out by a qualified neurosurgeon. Most surgeons operate using loupe magnification. The platysma muscle is separated or cleaved at the right side of the midline (less frequently on the left side), and the prevertebral space is reached by an approach medial to the sternocleidomastoid muscle and the carotid artery, and lateral to the trachea and oesophagus. The disc is incided and the corpora are distracted. Discectomy is performed as thorough as possible. Regularly the posterior ligament is cut and the spinal root is decompressed. If necessary, spondylarthrotic rims are removed. To the preference of the surgeon bone graft or an intervertebral fusion device is left behind. Decompression of more levels is allowed. If the surgeon prefers to decompress the cervical nerve root from the dorsal side it is allowed to perform a dorsal foraminotomy. The muscles of the neck are unilaterally detached at the site of interest. With a high-speed drill a foraminotomy is performed to decompress the nerve.

The postoperative care will be performed according to ‘usual care’ and will regularly be a stay in the hospital for one or two days, without physiotherapeutic treatment. If possible most patients will gradually return to work within weeks after the surgical intervention.

#### Group B: Conservative management

Management of the conservative arm will be performed according to usual care by either the neurologist or general practitioner (GP). In the Netherlands, formal guidelines for this approach are lacking, however, related guidelines for lumbar radicular syndrome exist. The treatment of CRS is aimed primarily at pain relief and maintenance/restoration of normal day-to-day activities. Various studies have shown that adequate and unambiguous information about the problem from which the patient is suffering (the nature of the condition) and what the patient can expect (the prognosis), together with trustworthy counselling can reduce the anxiety and uncertainty felt by the patients Usually, no soft collar nor physiotherapy is prescribed, however it is allowed. A graded activity time schedule is made beforehand together with the patient [24,25].

In case of progressive neurological deficit or worsening intolerable pain the GP or neurologist can refer the patient back to the research nurse or neurosurgeon in order to consider surgery. If, six months after randomisation, the patient has still not improved or suffers from disabling intermittent CRS, surgical treatment will be offered.

### Outcome assessment

Non-blinded examinations by the research nurse will take place at baseline, at 6 weeks, 3, 6, 9, 12, and 24 months after randomisation by visits and filling in questionnaires (Table 2). In addition, the patients will keep a diary. A second MRI will be made one year after randomisation of which the outcome will be told after the assessments. Data will be recorded and analysed at the Data Coordination Centre in Leiden.

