**Table 2 T2:** **Follow**-**up flowchart**

	**Intake**	**Operation**	**6w**	**3 m**	**6 m**	**8 m**	**12 m**	**24 m**
Demography & diagnosis	X							
Neurological examination	X	X	x		x		x	x
Informed consent	X							
MRI	X						x	
NDI	X		x	x	x	x	x	x
VAS pain/tinglings	X		x	x	x	x	x	x
SF-36	X		x	x	x	x	x	x
IPQ-K	X							
Perceived recovery	X		x	x	x	x	x	x
Health state utility VAS	X		x	x	x	x	x	x
DS-14	X		x	x	x	x	x	x
EuroQol	X		x	x	x	x	x	x
Diary	X		x	x	x	x	x	x
Re-operation			x	x	x	x	x	x
Complication			x	x	x	x	x	x

Overview of follow-up moments and received information (for explanation: see text).

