#### Secondary outcome measures

1. Neck Disability Index (NDI). Although the NDI is a score to monitor complaints of cervical myelopathy, it gives a reliable impression of the disability of the patient with respect to daily activities [28,29]. The scores of the items are added up and transformed into a scale of 0 to 100. A higher score reflects a better health condition.

2. VAS pain or tingling sensations in the arm at different time points (intake, 6 weeks and 3, 6, 8, 24 months).

3. VAS pain in the neck. The pain intensity in the neck will be measured with a 100 mm horizontal VAS at different time points (intake, 6 weeks and 3, 6, 8, 12, 24 months).

4. Short Form-36 (SF-36). The SF-36 will be used as a generic quality-of-life questionnaire. The questionnaire relates to the analysis of the general functional status of patients. The scores of the different topics are added up and transformed into a scale of 0 to 100. A higher score reflects a better health condition. The different topics can be summarised in a physical and psychological main domain.

5. Illness Perceptions Questionnaire – short form (IPQ-K). The Brief Illness Perceptions Questionnaire is translated from English to Dutch and adapted for differences in culture [30]. This questionnaire represents the way a patient copes with his complaints, and it gives insight in the functioning of a patient.

6. Perceived recovery. To measure perceived recovery a seven-point Likert scale will be used [31]. The scores on this scale vary from ‘completely recovered’ to ‘worse than ever’. The scales will be completed by the patient, research nurse, and the neurologist or neurosurgeon.

7. Health state utility VAS. Patients will assess how they value their health using a VAS ranging from 0 = as bad as death to 100 = perfect health.

8. DS-14. This Dutch questionnaire determines the extent of ‘Distressed-personality’ of the patient. A type D personality is defined in medical psychology as the co-existent presence of both negative affectivity (e.g. worrying, irritability, gloom) and social inhibition (e.g. reticence and a lack of self-assurance). The questionnaire consists of seven questions concerning negative affectiveness and seven questions concerning social inhibition. Individuals that score on both dimensions 10 or higher are being classified as having a type D personality. A type D personality has been demonstrated to have a negative influence on outcome of disease [32,33].

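### Complications are scheduled from randomisation rather than from surgery, so minor complications of late operations in the conservative arm may be recorded less completely than those of early operations

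*Protocol article*

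**What the plan says.** Follow-up runs on a calendar that starts at randomisation. Under Outcome assessment, the research nurse's examinations "will take place at baseline, at 6 weeks, 3, 6, 9, 12, and 24 months after randomisation by visits". Table 2 and the Secondary outcome measures section follow the same clock but put the fifth assessment at month 8, for example neck pain "at different time points (intake, 6 weeks and 3, 6, 8, 12, 24 months".

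In Table 2 the row "Complication" is marked at 6 weeks and at 3, 6, 8, 12 and 24 months, and is empty under Operation. The Operation column is in use: the row "Neurological examination" is marked there. No contact at a fixed interval after surgery is described for either arm.

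Operations occur at different points on that calendar. For group A, "Surgery will take place within 2–4 weeks of randomisation". For group B, "If, six months after randomisation, the patient has still not improved or suffers from disabling intermittent CRS, surgical treatment will be offered". Group B surgery can also come sooner: "In case of progressive neurological deficit or worsening intolerable pain the GP or neurologist can refer the patient back to the research nurse or neurosurgeon".

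Two other records are mentioned. A standardised form captures procedure variables and is described under Group A. A patient diary is kept, which the secondary outcome list describes as a cost diary that includes absenteeism. Neither is said to record complications. Complication frequency is the thirteenth listed secondary outcome, with no recall period and no window from surgery.

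**The concern.** The same operation carries much the same early post-operative risks whether it is done at week 3 or at week 29. On the published schedule, the time until someone asks about those risks depends on where the operation falls between visits, and that differs systematically by arm. Group A's surgery is timed to fall shortly before the 6-week visit, whereas group B's is not tied to any visit. A temporary complaint that has resolved before the next visit may be reported less reliably the longer the wait.

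The Conclusion and Discussion section expects fewer adverse events under prolonged conservative care. Any loss of minor events after late surgery would lower group B's count, which is the direction of that expectation. It would also affect any comparison of complication rates after early and late operations, a natural question in a trial that studies the timing of surgery.

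**Working it through.** The plan gives no figure of its own to reproduce here, so the check is calendar arithmetic.

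**Inputs**
- Visits, from Outcome assessment and Table 2: 6 weeks, then months 3, 6, 8 (Table 2) or 9 (text), 12 and 24.
- One month = 365.25 / 12 / 7 = 4.35 weeks. Month 3 is then week 13.0, month 6 week 26.1, month 8 week 34.8, month 9 week 39.1, month 12 week 52.2 and month 24 week 104.4.
- Group A surgery at weeks 2–4 (Group A section).
- Group B offer at month 6 (Group B section). The document gives no wait from offer to operation. I assume group A's 2–4 weeks, which puts surgery at 26.1 + 2 = 28.1 to 26.1 + 4 = 30.1 weeks.

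**Formula:** gap = week of next scheduled visit − week of surgery.

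| Operation | Week | Gap with month-8 visit | Gap with month-9 visit |
|---|---|---|---|
| Group A | 2–4 | 6 − 4 = 2 to 6 − 2 = 4 | the same |
| Group B, early referral (illustration) | 8 | 13.0 − 8 = 5.0 | the same |
| Group B, after the 6-month offer | 28.1–30.1 | 34.8 − 30.1 = 4.7 to 34.8 − 28.1 = 6.7 | 39.1 − 30.1 = 9.0 to 39.1 − 28.1 = 11.0 |
| Group B, four weeks before month 9 | 35.1 | about 17 (next visit is month 12) | 39.1 − 35.1 = 4.0 |
| Group B, just after month 12 | 52.2 | up to 104.4 − 52.2 = 52.2 | the same |

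Group A is also asked a second time at month 3, which is 13.0 − 4 = 9 to 13.0 − 2 = 11 weeks after surgery. On the month-9 schedule, group B's first enquiry after the planned offer comes as late as group A's second.

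Between months 6 and 12 the longest possible gap is 52.2 − 34.8 = 17.4 weeks on Table 2's schedule and 13.0 weeks on the text's. The month-8 versus month-9 conflict moves the first enquiry after the planned late operation by one month, about 4.3 weeks.

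**Post-operative time to month 24:** group A 104.4 − 4 = 100 to 104.4 − 2 = 102 weeks; group B after the 6-month offer 104.4 − 30.1 = 74 to 104.4 − 28.1 = 76 weeks.

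**Size of any loss:** this would need a complication rate, a rate of recall by elapsed time and the share of group B operated. The document gives none of them, so it cannot be computed.

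**The case against.** The strongest reply is that unequal gaps are not the same as missing events. Complications are an outcome counted over the whole trial and marked at every follow-up visit to month 24. Nothing says that a visit records only what is present that day, or that it relies on memory rather than hospital records. Between-visit reporting is also detail that a condensed article may leave to the full protocol, which is not shown. This stands against any claim that complications are in fact under-counted.

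A reader might infer three stronger things, and the document supports none of them.

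- *That complications are collected at no other point.* Table 2 has an operation-linked assessment, there is a procedure form and a diary, and a deteriorating group B patient may be sent back to the research nurse or neurosurgeon. The article does not say that these capture complications, but it does not exclude it. What can be said is that the published schedule marks complications at calendar visits alone.
- *That reoperations and serious complications are missed too.* These are hospital events, unlikely to be forgotten over the gaps shown here.
- *That the shorter post-operative time in group B biases the arm comparison.* The Conclusion and Discussion section presents the trial as a comparison of two strategies by intention to treat. Both arms are followed for the same 24 months from randomisation, and less time after a deferred operation is a consequence of the deferral strategy. It matters only for a rate per operation, which the article does not propose.

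The contrast also varies. A group B operation done 2–4 weeks before a visit has the same gap as group A, and the longest gaps need surgery after the one-year main assessment.

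What the reply does not remove is that how closely each operation's complications are looked for is not part of either strategy. The schedule has a place tied to surgery and does not use it for complications.

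**Conclusion.** The point holds as a possible, unequal ascertainment of minor or transient complications. On the published schedule the first marked enquiry comes 2–4 weeks after surgery in group A. In group B, after the 6-month offer, it comes about 5–7 weeks after surgery (month-8 visit) or 9–11 weeks (month-9 visit), and up to 52 weeks for surgery just after month 12. The group B figures for the 6-month offer rest on the assumed 2–4 week wait. The conclusion also assumes that the form and diary do not already capture complications of late operations, which the article leaves open.

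The effect on the complication count is of unknown size, and a loss is possible rather than demonstrated. If there is one, it would favour the expectation of fewer adverse events under conservative care. The primary outcome is untouched. This is a worthwhile, inexpensive improvement to a secondary safety outcome.

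**What to change.** 1. Mark complications in Table 2's Operation column, and state that the standardised procedure form, with a line for complications, is completed for every cervical operation in either arm.
2. Add one short complication enquiry, for example by telephone, at the same fixed interval after any operation. If the window covers the 2–4 weeks after surgery at which group A is already seen, the 6-week visit can serve for group A patients operated on schedule.
3. Report complications per operation within that common window as a descriptive supplement. Keep the by-arm intention-to-treat totals as the main safety comparison.
4. Reconcile the month-9 visit in Outcome assessment with month 8 in Table 2 and the secondary outcome list, since this is the first visit after the planned late-surgery point.

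The cost is one line on an existing form and one brief contact per late-operated patient. The document gives no late-surgery rate. If 30% of the 200 group B patients were operated late (an assumption), that is 0.30 × 200 = 60 contacts; each percentage point more or less changes this by 2, with a ceiling of 200. The drawback is that late-operated patients get a contact that others do not, which is why the per-operation table should stay supplementary. The change concerns data collection only.
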